## Abstract

**Background:**

Chronic insomnia (CI) is a mind-body disease that is commonly defined as a state of having disturbed daytime activities due to poor nighttime sleep quality. Baduanjin qigong (BDJQG) is widely used for CI in China. However, there is little scientific evidence to evaluate its effects on the hyperarousal state, which is closely associated with improved sleep quality.

**Objective:**

The objective of the trial is to assess the therapeutic effects of BDJQG on sleep quality in patients with CI.

**Methods:**

A randomized controlled trial will be conducted on 86 patients, who will be divided into a BDJQG group and a cognitive behavioral therapy for insomnia group at a ratio of 1:1. Interventions in both groups will be given to the participants 7 times a week for 8 weeks, and the participants will be followed up for 4 weeks. The primary outcome is the change in the Pittsburgh Sleep Quality Index from baseline to week 8. The secondary outcomes are the changes in the Hyperarousal Scale, Insomnia Severity Index, Fatigue Scale-14, wrist actigraphy, salivary cortisol level, and functional magnetic resonance imaging from baseline to week 8. All main analyses will be carried out on the basis of the intention-to-treat principle.

**Results:**

This study was funded from January 2023. As of the submission of the manuscript, there were 86 participants. Data collection began in April 2023 and will end in January 2024. Data analysis is expected to begin in January 2024, with the publication of results expected in February 2024.

**Conclusions:**

This study will present data concerning the clinical effects of BDJQG on CI. The results will help to demonstrate whether BDJQG is an effective therapy for improving sleep quality in association with a decreased hyperarousal level as a possible underlying mechanism. This study will provide much-needed knowledge for complementary and alternative therapy for patients with CI.

**Trial Registration:**

China Clinical Registration Agency ChiCTR2300069241; https://chictr.org.cn/bin/project/ChiCTR2300069241

**International Registered Report Identifier (IRRID):**

PRR1-10.2196/53501

## Introduction

Chronic insomnia (CI) is the most common clinical sleep disorder. It is characterized by persistent challenges in initiating or maintaining sleep; suboptimal sleep quality; and impairments in daytime functioning, including fatigue, attention deficit, and emotional instability [1]. The prevalence of CI in the general population varies between 9% and 12%, with transient insomnia symptoms reported by 22% to 35% of individuals [2]. The widely recognized classification framework for sleep disorders, the *International Classification of Sleep Disorders, Third Edition*, stipulates specific criteria for diagnosing CI. Specifically, the diagnosis of CI necessitates the presence of insomnia symptoms for a minimum duration of 3 months, with no fewer than 3 associated symptoms, which may encompass manifestations such as fatigue, irritability, and compromised work, school, or social performance [3]. While CI is classified as a sleep disorder, its pathophysiological underpinnings suggest a prevailing state of hyperarousal during both sleep and wakefulness phases [4]. Evidence of the hyperarousal phenomenon in individuals with insomnia encompasses elevated levels of cortisol and adrenocorticotropic hormone during the initial stages of sleep and discernible thalamic responses determined through functional magnetic resonance imaging (fMRI) [5].

Several pharmaceutical agents, including benzodiazepines, benzodiazepine agonists, and certain antidepressants, have demonstrated efficacy in the short-term management of insomnia [6]. However, these pharmacological interventions carry inherent risks related to the sedative properties. The risks encompass an elevated propensity for falls; cognitive confusion; and the potential for the development of tolerance, dependence, and withdrawal effects when used for extended periods [7]. Cognitive behavioral therapy for insomnia (CBTI), regarded as the first-line treatment for insomnia, has proven its effectiveness in addressing CI in adults. It consistently ameliorates clinical symptoms associated with insomnia, producing clinically meaningful effects [8]. Nevertheless, the accessibility of CBTI remains challenging for patients, primarily due to the limited availability of specialized practitioners, which hinders its ability to adequately meet clinical demands [9]. Several complementary and alternative medicine modalities, including traditional Chinese herbal medicine [10], acupuncture [11], and qigong, have exhibited efficacy in the treatment and prevention of insomnia, effectively mitigating symptoms such as fatigue and depression.

Qigong is a component of traditional Chinese medicine characterized by its integrated approach, involving breath control, physical movement, and meditation techniques. Notably, extant research has furnished evidence supporting the beneficial effect of qigong on various facets of health among individuals with insomnia, including the enhancement of sleep quality [12,13], alleviation of symptoms related to anxiety and depression [14,15], and modification of sleep-wake patterns as corroborated by actigraphy assessments [16].

The nomenclature “Baduanjin qigong” (BDJQG) was first documented in *Yi Jian Zhi* by Hong Mai during the Northern Song Dynasty, indicating that this mind-body practice has a history spanning over 800 years [17]. This modality is renowned for its holistic approach, characterized by facilitating overall coordination, unblocking meridians, harmonizing the mind and body, and assisting the body in achieving a relative equilibrium between the yin and yang elements. The safety and efficacy of BDJQG have garnered empirical support through numerous clinical trials, rendering it a widely embraced therapeutic approach for diverse chronic ailments [18-20]. For example, an illustrative meta-analysis has indicated that BDJQG, particularly when integrated with mindfulness techniques, is effective in alleviating musculoskeletal pain and enhancing the overall sleep quality in individuals with chronic conditions [21]. Furthermore, BDJQG comprises 8 distinct movements that are easy to learn. If its efficacy is proven, its wider use could be promoted.

Previous investigations into insomnia treatment have primarily centered on enhancing sleep quality but have often overlooked the assessment of daytime functioning. In contrast, our previous research findings suggested that qigong exhibits efficacy both in ameliorating sleep quality and in enhancing daytime functioning [22].

Remarkably, assessments of the hyperarousal state have been conspicuously scarce in previous trials. In this study, we intend to comprehensively evaluate hyperarousal from a multidimensional perspective, encompassing cognitive functions (evaluated through the Hyperarousal Scale [HAS]), cortical activities (scrutinized through fMRI), and hypothalamic-pituitary-adrenocortical (HPA) axis functioning. Salivary cortisol level (SCL), known to correlate with various sleep parameters [23], will be measured, given that hyperarousal in insomnia is associated with heightened cortisol secretion. Previous empirical evidence has directly indicated that BDJQG may induce changes such as increased melatonin levels and decreased cortisol levels, which are indicative of reduced wakefulness-related factors [24]. These physiological markers will be meticulously monitored as potential indicators of BDJQG’s effect on the HPA axis.

Building upon the insights gleaned from previous research and considering the plausible role of BDJQG in attenuating hyperarousal, we have formulated a randomized, open-label, parallel-controlled trial to systematically investigate the therapeutic efficacy of BDJQG concerning both sleep quality and hyperarousal state in individuals with CI.

## Methods

### Aims and Study Design

The primary objectives of this open-label, parallel, noninferiority randomized controlled trial (RCT) will be 2-fold:

To ascertain whether BDJQG can yield improvements in the primary outcome, which is sleep quality, and the secondary outcomes, encompassing an array of measures spanning various domains, including hyperarousal state, severity of insomnia, and levels of fatigue. These improvements will be evaluated in comparison to CBTI.To explore the potential efficacy of BDJQG as a therapeutic intervention for CI and its potential association with a reduction in hyperarousal levels, which may serve as an underlying mechanistic pathway. This exploration will be facilitated through correlation analyses.

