### Sample Size

The following 2 hypotheses are related to the differences between the 2 groups:

Hypothesis 1: μ_1_= μ_2_Hypothesis 2: μ_1_≠ μ_2_,

where μ_1_ is the PSQI mean score of the 8-week treatment in the BDJQG group, and μ_2_ is the PSQI mean score of the 8-week treatment in the CBTI group.

The required sample size has been calculated using an estimation formula based on the difference between 2 sample means and SDs (PSQI, which is assessed using composite points of sleep quality). Therefore, in a study with this sample size, the difference between the BDJQG group and the CBTI group will be considered, and the conservative comparison method by Bonferroni will be adopted. In this study, it is expected that the BDJQG group will be 1.78 points better than the CBTI group in the PSQI scale mean score. The final calculated difference and SD of the 2 groups of the PSQI mean scores were calculated [40]. On the basis of 0.9 power to detect a significant difference (α=.025; 1-sided), 34 participants will be required for each group.

The following formula was used to calculate the sample size in this trial:

[figure not shown]

Given that an attrition rate of ~20% is anticipated, our target enrollment will be 43. Therefore, a total of 86 participants should be recruited for this RCT.

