### Randomization and Blinding

Following a postbaseline assessment, the eligible participants will be randomly allocated to the BDJQG group and the CBTI group, adhering to a 1:1 equal proportion allocation. A randomization list will be meticulously generated by a skilled statistician using a computer program (Strategic Applications Software, version 9.1.3; SAS Institute Inc). The generated random sequences will be sequentially numbered by the statistician, who serves as the architect of the randomization sequence. Subsequently, the sequences will be placed within opaque envelopes by a designated project manager, uninvolved in the recruitment process. These sealed envelopes will ultimately be delivered to the research team.

Before implementing the random assignment procedure, the research team will diligently record the particulars of each participant at the clinical center. These records will encompass the participant’s information, such as name, date of birth, participant and center codes, and the inclusion date. Following a meticulous review of the participant’s information by the research team to ascertain eligibility, a sequence will be randomly drawn from the envelope. The selected sequence will be applied to label the participant’s data, designating the participant’s assignment to one of the study groups. This information will then be conveyed to the respective participants.

It is noteworthy that, due to the specific nature of the intervention approach, this study is an open trial, with only the statistical analysis experts being kept blinded, as delineated in the research conducted by Cheng et al [41].

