### Statistical Analysis

The collected data will meticulously be entered into Microsoft Excel (Microsoft Corporation), and subsequent statistical analysis will be conducted using SPSS software (version 18.0; SPSS Inc). Continuous variables will be summarized using the mean value and SD, with the median and IQR used for variables exhibiting nonnormal distributions. Categorical variables will be presented as frequencies or percentages.

For within-group comparisons, paired 2-tailed *t* tests will be used. Between-group differences will be analyzed through 2-sample, independent-sample *t* tests, with effect sizes computed using Cohen *d* statistics. Furthermore, demographic characteristics, baseline measurements, and changes in measurements from baseline to study completion between the 2 groups will be analyzed using 2-sample, independent-sample *t* tests. In cases where baseline measurements exhibit disparities, analysis of covariance will be implemented to account for these variations when comparing the 2 groups.

The clinical overall efficacy evaluation will be based on a nonparametric test for 2 independent samples. In instances of limited participant numbers within a specific subject or in the presence of missing data, the Mann-Whitney *U* test will be used to assess differences between the groups. A statistical significance level of *P*<.05 will be used, signifying statistical significance when this threshold is met.

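### The trial is labelled noninferiority, but its hypotheses, sample size and test are all for a difference and no margin is stated, so a noninferiority conclusion would have no valid basis

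*Protocol article*

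**What the plan says.** The design label is in the protocol article, Aims and Study Design: "The primary objectives of this open-label, parallel, noninferiority randomized controlled trial (RCT) will be 2-fold". The first aim in that section asks whether BDJQG improves sleep quality and the secondary outcomes, and adds "These improvements will be evaluated in comparison to CBTI". It does not say that BDJQG should be no worse than CBTI by some amount.

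Sample Size defines the two means as the PSQI scores at 8 weeks in each group. It sets equality against "Hypothesis 2: μ_1_≠ μ_2", with no margin term. The effect assumption is that "it is expected that the BDJQG group will be 1.78 points better than the CBTI group in the PSQI scale mean score". The power statement is "On the basis of 0.9 power to detect a significant difference (α=.025; 1-sided), 34 participants will be required for each group". The SD is attributed to a cited source and not given as a number.

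Statistical Analysis then says "Between-group differences will be analyzed through 2-sample, independent-sample *t* tests, with effect sizes computed using Cohen *d* statistics", with significance declared at P<.05. It compares no confidence limit with a margin.

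The word noninferiority occurs only in Aims and Study Design. The Abstract calls the study a randomized controlled trial, and the end of the Introduction describes a randomized, open-label trial with parallel groups.

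**The concern.** A noninferiority trial has to reject the hypothesis that the new treatment is worse than the control by at least a stated margin. A test of equality cannot do that. Failing to reject equal means shows only that the data did not separate the arms. It does not bound how much worse BDJQG might be.

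The comparator makes this important. The Introduction calls CBTI the first-line treatment, so similar performance is a plausible and publishable result, and it is the result that a noninferiority label anticipates. In that case the plan offers a P value above .05 under a noninferiority heading, with no rule for reading it. The way is then open to report BDJQG as noninferior to first-line therapy on evidence that cannot support the claim.

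Timing adds to the problem. All 86 participants were enrolled when the article was submitted (Results), and the trial is open-label. A margin introduced now would need clear justification, and evidence that it was chosen without sight of outcomes by group.

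**Working it through.** **Side-by-side reading**

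| Element | A noninferiority design needs | The article states |
|---|---|---|
| Null hypothesis | BDJQG worse than CBTI by at least a margin M | equal means |
| Expected difference | usually 0, set against M | 1.78 points in favour of BDJQG |
| Power | to exclude M | to detect a difference |
| Decision | upper 97.5% confidence bound below M | t test, P<.05 |
| Margin | a number with a justification | none stated |

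Every row disagrees with the label. This needs no calculation.

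**Inputs for the size of the problem** (Sample Size): difference 1.78, power 0.90, one-sided α .025, 34 per arm, attrition about 20%. The SD is not stated, so the 34 cannot be reproduced independently. It can be solved backwards.

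1. Standardised difference implied by 34 per arm: d = (1.96 + 1.2816) × √(2/34) = 0.786.
2. Implied SD = 1.78 / 0.786 = 2.264. Because n is rounded up, any SD from about 2.23 to 2.26 gives 34. An SD of 2.0 would give 27 per arm, 2.5 would give 42 and 3.0 would give 60.
3. Attrition: 34 / 0.8 = 42.5, rounded up to 43 per arm, 86 in total. This reproduces.
4. Standard error with 34 per arm: 2.264 × √(2/34) = 0.549. The 95% CI half-width is 1.96 × 0.549 = 1.08 points.

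**How often the planned test is nonsignificant** (two-sided .05, normal approximation), for a true difference δ: Φ(1.96 − δ/0.549) − Φ(−1.96 − δ/0.549).

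- δ = 0: 95%.
- BDJQG 0.89 points worse (half of 1.78): 63%.
- BDJQG 1.0 point worse: 56%.
- BDJQG 0.89 points better: also 63%, so superiority power is 37%.

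**Noninferiority power with 34 per arm and true difference 0**: Φ(M/0.549 − 1.96). The margins are assumptions, since the article gives none. The n for 90% power is 2 × (2.26 × 3.2415 / M)², rounded up.

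| Assumed margin M | Power at 34 per arm | Evaluable n per arm for 90% power |
|---|---|---|
| 0.5 | 15% | 430 |
| 0.89 | 37% | 136 |
| 1.0 | 44% | 108 |
| 1.5 | 78% | 48 |
| 1.78 | 90% | 34 |
| 2.0 | 95% | 27 |

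**Sensitivity to the SD** (34 per arm): for SDs from 2.0 to 3.0, noninferiority power at margin 1.0 runs from 54% down to 28%. The chance of a nonsignificant result when BDJQG is 1.0 point worse runs from 46% up to 72%. If all 43 per arm were analysed at SD 2.264, the standard error is 2.264 × √(2/43) = 0.488 and those two figures become 54% and 46%.

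**The case against.** The strongest defence is that the label is a single stray word. The endpoint, hypotheses and test are all stated, no other section claims noninferiority, and nowhere does the article plan to read a nonsignificant P value that way. If superiority is shown, noninferiority follows for any margin. The last point is right and limits the harm to the case where superiority is not shown. But the word stands in the sentence that defines the design and introduces the primary objectives, and it contradicts what follows. Whether or not misuse is planned, the article must say which question it answers.

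A second defence is that a margin may exist elsewhere: the sample-size formula is a figure that is not shown, and the article condenses a fuller protocol. One-sided .025 is also the usual noninferiority level, and 34 per arm would result equally if 1.78 were a margin with true difference 0. It is fair to say only that no margin is stated in this article. However, the text calls 1.78 an expected advantage and writes out hypotheses without a margin. A margin held elsewhere would contradict this section, so it would still need correcting.

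Third, the percentages depend on a back-solved SD, a t test and 34 evaluable per arm. Statistical Analysis brings in the Mann-Whitney test when data are missing, and the Abstract promises intention-to-treat analysis, which could mean more than 34 per arm. This stands: the figures are illustrations. The contradiction does not depend on them.

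Finally, analysis had not begun and the statistical analysts are blinded. That makes correction still possible; it does not make it unnecessary.

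**Conclusion.** The concern holds. The design label is contradicted by the hypotheses, the effect assumption, the power statement and the test, and the article gives no margin or confidence-bound rule. As written, the trial can support a superiority conclusion but not a noninferiority one. This should be settled before analysis because it decides what the trial may conclude.

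On the implied SD of about 2.26 with 34 evaluable per arm, a nonsignificant result is compatible with BDJQG being appreciably worse: it would occur 56% of the time at a true deficit of 1.0 PSQI point. The stated 90% power carries over to noninferiority only if the margin is at least 1.78 and the true difference is 0. These sizes rest on the back-solved SD, the normal approximation and assumed margins. The finding itself rests only on the text.

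**What to change.** Make the document describe one design.

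**Preferred:** since the hypotheses, sample size and test all address a difference, delete noninferiority from Aims and Study Design and declare a superiority trial. Report the BDJQG-minus-CBTI difference in week-8 PSQI points with its 95% CI. Week 8 is how Sample Size defines the means; under randomisation the change from baseline, the declared primary outcome, has the same expected difference. State that a nonsignificant result will not be reported as noninferior or equivalent. In the same edit, align the two-sided alternative and one-sided .025 in Sample Size with the plain P<.05 in Statistical Analysis.

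**If noninferiority is truly intended:** fix and justify a margin before the analyst sees any outcome data, and document when that was done. Replace the null hypothesis with a BDJQG-minus-CBTI difference at or above the margin. Base the decision on the upper 97.5% confidence bound. Restate the power for that margin with an expected difference of 0, and give the SD.

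**Cost:** the first option is a wording change before database lock, needs no extra patients and gives up the noninferiority claim. The second also needs only text, but the stated power becomes less favourable for any margin below 1.78. Keeping 90% power at a margin of 1.0 would take about 108 evaluable per arm at the implied SD.

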### Study Setting

Participants will be recruited from the Shanghai Municipal Hospital of Traditional Chinese Medicine. Eligibility for inclusion will be determined by 2 orthopedic surgeons based on predefined inclusion and exclusion criteria. Participants who are determined to be eligible and provide written informed consent will be randomly allocated to either the BDJQG group or the CBTI group in a 1:1 ratio. The BDJQG group will undergo BDJQG treatment, while the CBTI group will receive cognitive behavioral therapy for insomnia. Both groups will undergo an 8-week-long treatment program, consisting of 1 supervised session per week at Shanghai University of Traditional Chinese Medicine and the remaining 6 days of the week completed at home. The study will span a total of 13 weeks, comprising a 1-week-long screening period, an 8-week-long treatment phase, and a subsequent 4-week-long follow-up period.

Assessments using various scales will be conducted at baseline, the 4-week intervention mark, the 8-week intervention mark, and the 4-week follow-up. SCL will be measured at baseline, the 4-week intervention mark, and the 8-week intervention mark. Actigraphy and fMRI assessments will be administered at baseline and the 8-week intervention mark. Figure 1 gives a visual representation of the research process, and Table 1 shows an overview of the study’s time points.

**Figure 1 figure1:**
[figure not shown]
Flowchart of the study design. BDJQG: Baduanjin qigong; CBTI: Cognitive behavioral therapy for insomnia; fMRI: functional magnetic resonance imaging; FS-14: Fatigue Scale-14; HAMD: Hamilton Depression Scale; HAS: Hyperarousal Scale; ISI: Insomnia Severity Index; PSQI: Pittsburgh Sleep Quality Index.

**Table 1 table1:** Chart of the trial’s time points.

Research process	Baseline (week 0)	Intervention period (weeks 1-8)	Intervention period (week 4)	Intervention period (week 8)	Follow-up (week 12)
Inclusion criteria	✓				
Exclusion criteria	✓				
Informed consent	✓				
Randomization and allocation	✓				
Intervention		✓			
PSQI^a^	✓		✓	✓	✓
HAMD^b^	✓		✓	✓	✓
ISI^c^	✓		✓	✓	✓
HAS^d^	✓		✓	✓	✓
FS-14^e^	✓		✓	✓	✓
Actigraphy	✓			✓	
Salivary cortisol	✓		✓	✓	
fMRI^f^	✓			✓	
Adverse events		✓		✓	✓
Working practice record		✓		✓	✓

^a^PSQI: Pittsburgh Sleep Quality Index.

^b^HAMD: Hamilton Depression Scale.

^c^ISI: Insomnia Severity Index.

^d^HAS: Hyperarousal Scale.

^e^FS-14: Fatigue Scale-14.

^f^fMRI: functional magnetic resonance imaging.

